#### Secondary

Participant experience and satisfaction of the CDCC services at 3 and 12 months.Differences in the changes in mean BP or HbA1c between CDCC and non-CDCC participants with HT, pre-DM and/or DM from baseline to 12 months.Costs for the implementation and operation of the CDCC Pilot Scheme in its pilot phase (1–2 years).

### Data analysis

The proportion of patients and/or service providers achieving the standards of care, participant experience, satisfaction and enablement, and the costs of the CDCC Pilot Scheme and the direct medical costs from the participants at 12 months will be described with descriptive statistics. Differences in the proportion of participants reaching the targeted disease control outcomes between CDCC and non-CDCC participants will be compared using chi-squared tests, and adjusted for confounding factors by logistic regression. Changes in clinical parameters from baseline to 12 months will be compared between CDCC and non-CDCC participants by paired t-tests. The total mean costs on each CDCC and non-CDCC participant will be compared using t-tests. The additional costs required for an additional participant in the CDCC Pilot Scheme to achieve target outcomes of disease control after 12 months will be reported as the ICER, calculated as the incremental cost incurred for each participant of the CDCC Pilot Scheme divided by the difference in the proportion of participants meeting targeted disease outcome. Cost-effectiveness of the Scheme would be determined by comparing the ICER to the willing-to-pay threshold of 1 GDP per year.

All statistical analyses will be performed using Stata (version 15.1). A p-value < 0.05 is considered statistically significant.

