## Methods

### Study design

This study consists of three parts. First, the evaluation of the quality of care is a cross-sectional study including site visits at DHC/DHC Express, administration of two serial quality of care questionnaires at 6 and 12 months among service providers, and extraction of the Scheme operational data from the eHealth database and DHC IT module, which are electronic databases used by the DHC/DHC Express to record participant data. Second, the evaluation of participant acceptability is a longitudinal cohort study by telephone surveys among CDCC participants at 3 and 12 months after CDCC enrolment. Third, the evaluation of the effectiveness and cost-effectiveness is a 1-year comparative cohort study using longitudinal data on health outcomes and healthcare utilization (and hence direct medical costs) among CDCC and non-CDCC participants at baseline and 12 months. Costing questionnaires on the set-up and operation costs of the Scheme will be distributed among service providers.

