### Subjects

To evaluate the quality of care, all operators of the DHC/DHC Express, and selected FDs and allied health professionals, will be asked to complete quality of care questionnaires. All participants who have enrolled into the CDCC Pilot Scheme between 1 Jan and 30 Jun 2024 will be included in the evaluation of the standards on process and outcome of care.

A convenient sample of 548 CDCC participants would be recruited from all 18 DHC/DHC Express between 1 Apr 2024 and 31 Aug 2024 to complete a survey on self-reported outcomes on participant acceptability and enablement. A conservative target of 140 participants for each diagnosis (i.e., normal, pre-DM, HT and DM) will be set to ensure different patients are equally represented.

The effectiveness and cost-effectiveness of the Scheme will be evaluated by comparing the differences in health outcomes and healthcare utilization rates among CDCC and non-CDCC participants at 12 months after enrolment. Records for CDCC participants enrolled between 1 Jan and 30 Apr 2024 who meet the inclusion criteria to participate in the CDCC Pilot Scheme will be included as the intervention group, while participants in the comparison group would be non-CDCC participants recruited in the community through collaboration with local networks and organizations. Participants ≥ 45 years, without a known diagnosis of HT and/or DM, and provide informed consent are eligible to join the study.

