### Sample size calculation

The sample size needed for evaluating participant acceptability is based on the proportion of participants who showed an increase in enablement, measured by the Patient Enablement Instrument (PEI), one year after enrolment into the CDCC Pilot Scheme. Previous studies showed that 55.6–72.2% of participants reported PEI score > 0 after entering structured programmes for DM and/or HT [10–12]. Assuming the proportion of CDCC participants with PEI score > 0 at 12 months to be 50%, 383 CDCC participants are required with 5% margin of error and significance level of 5%. To allow for about 30% attrition, the sample size required will be 548.

The sample size for evaluating the effectiveness and cost-effectiveness was determined based on the difference in the proportion of patients achieving the targeted outcome for disease control after 12 months between CDCC participants and the comparison group. Previous studies evaluating the 12-month effectiveness of the multi-disciplinary Risk Assessment and Management Program for DM or HT implemented in public primary care in Hong Kong found that the proportion of participants achieving treatment target (glycated hemoglobin [HbA1c] < 7.0% or systolic/diastolic blood pressure [BP] < 140/90mmHg) increased by 5.40% [13] or 1.18% [14], respectively after 12 months, compared to patients receiving usual care. Assuming a conservative 3% increase in the proportion of participants achieving treatment target after 12 months in the CDCC group, a total of 378 participants with pre-DM, HT and/or DM are required to detect difference at a power of 80% with a significance level of 5%/ According to the Hong Kong Population Health Survey 2020, the prevalence of undiagnosed HT and DM among individuals aged 45–84 was 15.4% and 4.6%, respectively [15]. Previous studies reported that the prevalence of pre-DM was 2.3–8.9% in Hong Kong [15, 16]. Taking a prevalence of approximately 20% in total for pre-DM, HT and/or DM, and accounting for an attrition of 30%, a total of 1,886 non CDCC participants will be required.

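### The paired t-test named for comparing BP and HbA1c changes between CDCC and non-CDCC participants cannot be run on two unmatched cohorts and does not test the stated secondary outcome

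*Protocol article*

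**What the plan says.** The list of secondary outcomes in the protocol article includes "Differences in the changes in mean BP or HbA1c between CDCC and non-CDCC participants with HT, pre-DM and/or DM from baseline to 12 months". The target is therefore a contrast between groups: how far the mean change in one cohort departs from the mean change in the other.

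For this outcome the Data analysis section gives one rule: "Changes in clinical parameters from baseline to 12 months will be compared between CDCC and non-CDCC participants by paired t-tests".

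The design sections describe who is being compared. Under Study design, "the evaluation of the effectiveness and cost-effectiveness is a 1-year comparative cohort study using longitudinal data on health outcomes and healthcare utilization". Under Subjects, the intervention group consists of "Records for CDCC participants enrolled between 1 Jan and 30 Apr 2024" who meet the Scheme's inclusion criteria, while "participants in the comparison group would be non-CDCC participants recruited in the community through collaboration with local networks and organizations". The Sample size calculation section says that "a total of 1,886 non CDCC participants will be required"; it sets no equal or paired number of CDCC participants.

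Two nearby rules in Data analysis help with interpretation. The comparison of proportions reaching disease control is to be "adjusted for confounding factors by logistic regression". For costs, "The total mean costs on each CDCC and non-CDCC participant will be compared using t-tests", with no mention of pairing.

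**The concern.** The sentence joins a between-group comparison to a test that works on pairs. Pairs exist in this study only within a person (baseline and 12 months), not across the two groups. Taken literally, the analysis cannot be carried out. Taken as two before-after tests, one per group, it can be carried out but answers a different question: whether each group changed, not whether the groups changed by different amounts.

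At stake is how the secondary BP and HbA1c results would be read. Two separate before-after p-values invite the reading that a significant change in one group and a non-significant change in the other shows an effect of the Scheme. That inference is invalid, because the difference between the two changes has not been tested. Before-after results are also hard to interpret here. The outcome concerns people with HT, pre-DM and/or DM, and eligibility requires no known diagnosis of HT and/or DM at entry. Many will have been identified because a value was raised, so some fall by regression to the mean can be expected without any intervention. Only a direct contrast with a comparison group addresses that.

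**Working it through.** No sample size, power or significance level in the protocol is derived from the paired t-test, so there is no stated figure to reproduce. The check has two parts.

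**1. Is there any pairing between the groups?**

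- Source: Scheme records for one group and community recruitment for the other (Subjects).
- Size: 1,886 is fixed for the comparison group. No CDCC number is fixed for this comparison (Sample size calculation).
- Confounding control: regression adjustment of the binary outcome (Data analysis). Individual matching is mentioned nowhere in the article.

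A paired t-test uses d_i = x_i - y_i for pair i, with t = mean(d) / (SD(d)/√n). With no rule linking a CDCC person to a non-CDCC person, d_i is undefined across groups. With unequal numbers the calculation fails outright: a standard routine given 200 and 264 values returns a shape error. The only d_i available is the 12-month value minus the baseline value within a person.

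**2. What could happen if two within-group tests were contrasted?**

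Inputs:

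- Number per group: 1,886 recruited x 0.20 prevalence x (1 - 0.30) retained = 264. The three factors are in the Sample size calculation section. Using 264 for the CDCC group as well is an assumption. The figure counts all participants with pre-DM, HT and/or DM, so those contributing to a BP analysis in HT alone would be fewer.
- SD of change in systolic BP: 15 mmHg (assumed; not in the document).
- Same true change in both groups, so no Scheme effect: 1 to 4 mmHg (assumed).
- Two-sided 5% level. The document gives p < 0.05 without stating sidedness.

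Standard error of a mean change: 15/√264 = 0.923 mmHg. Power P of one within-group test comes from the non-central t distribution with 263 degrees of freedom and non-centrality change/0.923. As the groups are independent, the probability that CDCC is significant and the comparison group is not is P x (1 - P).

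| Common true change | Non-centrality | P (one group) | CDCC-only significance, P(1 - P) |
|---|---|---|---|
| 1 mmHg | 1.08 | 19.0% | 15.4% |
| 2 mmHg | 2.17 | 57.9% | 24.4% |
| 3 mmHg | 3.25 | 89.9% | 9.1% |
| 4 mmHg | 4.33 | 99.1% | 0.9% |

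With no change at all, P = 5% and the figure is 0.05 x 0.95 = 4.8%.

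A simulation (5,000 runs, common change of 3 mmHg, SD 15, 264 per group) agrees. One group was significant and the other not, in either direction, in 18.8% of runs, against 2 x 9.1% = 18.2% from the table. In the same runs a Welch t-test on the change scores rejected in 5.5%, close to the nominal 5%. The direct test therefore has the right error rate in the setting where contrasting the two within-group results does not.

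**The case against.** The best defence is that the word paired is a slip. The sentence on costs uses plain t-tests for the same two groups, and the secondary outcome is correctly worded as a between-group difference. A paired test cannot be run across unmatched groups, so the mistake would surface at analysis. This is plausible, but the sentence as written still fixes an unsuitable test. It could equally be resolved at analysis into two before-after tests, which run without any error message.

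Several stronger readings are tempting, and the document does not support them.

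- *The team intends to contrast within-group p-values.* The article does not say so. That consequence is conditional on how the sentence would be carried out.
- *A spurious one-sided pattern is the likely result.* It is not likely in general. With the inputs above the probability runs from under 1% to 24% over common changes of 1 to 4 mmHg, and every row rests on an assumed SD and an assumed CDCC group size.
- *The main conclusions of the evaluation are affected.* They are not. Disease control, a primary outcome, has a chi-squared test with adjusted logistic regression, the ICER does not use this test, and no sample size rests on it.
- *Leaving this comparison without covariate adjustment is itself an error.* Adjustment of a secondary continuous outcome is commonly left to a fuller document, which is not shown. It bears on the choice of replacement, not on whether the sentence is wrong.

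**Conclusion.** The point holds in a narrow form. The protocol assigns a paired t-test to a comparison between two separately sourced, unmatched cohorts. That test cannot be run between the groups, and the version that can be run does not test the secondary outcome. This is a wrongly stated rule, not a missing detail, and the conclusion needs no numerical assumption.

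Severity is moderate. The outcome is secondary. The possible damage is to the interpretation of BP and HbA1c changes, and its size cannot be pinned down from the document: the illustrative 15%, 24% and 9% at 1, 2 and 3 mmHg depend on the SD of 15 mmHg, 264 per group and an identical true change in both groups.

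**What to change.** Replace the sentence in Data analysis with a direct between-group comparison of change.

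- Minimum: an independent-samples (Welch) t-test on each participant's change from baseline to 12 months, with the mean difference and its 95% CI.
- Preferred, because the groups are not randomised: a linear regression of the 12-month BP or HbA1c value on group, with the baseline value and the same confounders as the logistic model, reporting the adjusted mean difference with 95% CI.

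Name one of the two as the main analysis of this outcome in advance, since in non-randomised groups an analysis of change scores and one adjusted for baseline can estimate different quantities. Keep paired t-tests, if wanted, for describing change within each group only, with a statement that they are not used to infer a difference between groups.

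The cost is one sentence. Baseline and 12-month data are already planned for both groups, and the Discussion reports that recruitment of the comparison group was still in progress, so the change can be made before analysis without further data collection.

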#### Evaluation of the effectiveness and cost-effectiveness

Anonymous data including demographics, diagnoses, prescriptions and laboratory tests (e.g. full lipid profile and renal function test) at baseline and 12 months for CDCC participants will be extracted from the eHealth database and DHC IT module, whereas those for non-CDCC participants will be collected via a telephone survey by an independent professional survey provider, and they will complete the screening blood test at a designated laboratory. With the exception of critical results that requires immediate medical attention, participants of the comparison group will be asked to follow up on any abnormal results on their own.

Costs of the CDCC Pilot Scheme composes the of implementation and operation costs by health service providers and the direct medical costs of participants. The total costs of implementing CDCC services will include all expenditure incurred from setting up the programme until 31 Dec 2024, while ongoing operational costs would be collected over a 1-year period from Dec 2023– Dec 2024 (Appendix C). Costs will be collected from each DHC/DHC Express, a representative sample of service providers and the Primary Healthcare Commission at 12 months using a costing questionnaire.

Direct medical costs refer to the ongoing costs on utilization of public and private healthcare services (including hospitalization, Accident & Emergency department, General Out-patient Clinics, and Specialist Out-patient Clinics) for both CDCC and non-CDCC participants, as well as the co-payment for the CDCC services among CDCC participants, within 12 months from enrolment. The information will be extracted anonymously from the Hospital Authority’s eHealth database and Clinical Management System, and collected from participants through telephone survey at 12 months (Appendix D). The cost of public healthcare service utilization will be estimated by multiplying the frequency of utilization with the unit cost published in the Gazette and Hospital Authority ordinance (Chap. 113) of charges for non-entitled persons for each public healthcare service.

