### Outcome measures

#### Primary

The proportion of participants and service providers achieving each criterion of the evaluation framework.Participant enablement measured by the PEI at 3 and 12 months.Differences in the proportion of CDCC and non-CDCC participants achieving the targeted disease control outcome after 12 months (systolic/diastolic BP < 140/90mmHg for HT, reduced HbA1c for pre-DM, HbA1c < 7% for DM).Differences in health service utilization rate and direct medical costs of CDCC and non-CDCC participants within 12 months from enrolment.The ICER for achieving the targeted outcomes for disease control.

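### The ICER's cost part is unadjusted in a non-randomised comparison, and as worded its cost and effect parts need not describe the same participants

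*Protocol article*

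**What the plan says.** All of this is in the Protocol article.

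- **ICER formula (Data analysis):** the "incremental cost incurred for each participant of the CDCC Pilot Scheme divided by the difference in the proportion of participants meeting targeted disease outcome".
- **Costs (Data analysis):** "The total mean costs on each CDCC and non-CDCC participant will be compared using t-tests". No covariate adjustment is named.
- **Effect (Data analysis):** the proportions at target "will be compared using chi-squared tests, and adjusted for confounding factors by logistic regression". The text does not say whether the crude or the adjusted result goes into the ICER.
- **Decision rule (Data analysis):** "Cost-effectiveness of the Scheme would be determined by comparing the ICER to the willing-to-pay threshold of 1 GDP per year".
- **Target (Outcome measures, Primary):** "systolic/diastolic BP < 140/90mmHg for HT, reduced HbA1c for pre-DM, HbA1c < 7% for DM". No target is defined for a normal screening result.
- **Who is in the Scheme (Subjects):** entry is for "Participants ≥ 45 years, without a known diagnosis of HT and/or DM", so diagnosis follows screening. The survey sample is set at "140 participants for each diagnosis (i.e., normal, pre-DM, HT and DM", which shows that Scheme participants include people who screen normal.
- **Allocation (Subjects):** the intervention group is drawn from Scheme records. The comparison group is recruited in the community through local networks and organisations.
- **Status:** the ICER and the between-group difference in direct medical costs are both primary outcomes.

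**The concern.** Two features of the stated analysis pull the ICER away from what it is meant to measure, the extra cost of one more participant reaching target.

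First, the plan recognises confounding for the effect but not for the costs. People who join a subsidised private-sector scheme may differ from community recruits in health, income and habitual use of services, and each of these can drive medical costs. A t-test on mean costs takes all such differences as the cost of the Scheme. This touches two primary outcomes: the cost comparison itself and the ICER.

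Second, the numerator is worded per Scheme participant, while the denominator can be computed only among people with a diagnosis. Cost per enrolee divided by effect per diagnosed person is not a cost per additional success. The ratio then comes out too low, which makes the Scheme look more cost-effective than it is.

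The hypothesis that the Scheme is cost-effective is decided by setting this ratio against a threshold, so either problem could change the conclusion.

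**Working it through.** **No figure to reproduce.** The article states no ICER and no costs. The check therefore uses symbols:

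- C = incremental cost per enrolee (not given).
- d = difference in proportion at target among diagnosed participants; 0.03, the planning value in Sample size calculation.
- q = diagnosed share of Scheme enrolees (not given). The same section uses about 20%, but to size the non-CDCC sample. A range of 20% to 80% is assumed here.

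**1. Population mismatch.** Read as worded, with cost over all enrolees and effect among the diagnosed, the ICER is C/d = C/0.03 = 33.3 × C.

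Now put both parts on all enrolees. Assume that people who screen normal contribute no effect and that the diagnosed share is the same in both groups. The effect per enrolee is q × d, and the ICER is C/(q × d).

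| q (assumed) | q × d | ICER, all enrolees | Ratio to the worded form (1/q) |
|---|---|---|---|
| 20% | 0.006 | 166.7 × C | 5.0 |
| 30% | 0.009 | 111.1 × C | 3.3 |
| 50% | 0.015 | 66.7 × C | 2.0 |
| 80% | 0.024 | 41.7 × C | 1.25 |

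The direction is the same throughout; only the size depends on q. An ICER restricted to diagnosed participants cannot be computed, because no costs by diagnosis are given.

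**2. Confounding of the numerator.** If the unadjusted cost difference is off by an amount B, the ICER moves by B/d. At d = 0.03 each unit of cost bias shifts the ICER by 33.3 units. The article gives no basis for the size or sign of B.

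**3. Confounding of the denominator, if the crude difference is used.** With a bias b on a true difference of 0.03, the ICER is multiplied by 0.03/(0.03 + b). The values of b are illustrative.

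| b (points) | Denominator | ICER multiplied by |
|---|---|---|
| −3 | 0 | undefined |
| −2 | 0.01 | 3.0 |
| −1 | 0.02 | 1.5 |
| +1 | 0.04 | 0.75 |
| +2 | 0.05 | 0.6 |

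**4. Why a point ICER is a weak basis for the decision.** Assume 378 diagnosed participants analysed in each group, which is generous because the article gives 378 as a total. Assume also a control rate of 50%, since none is stated. The standard error of a 3-point difference is √(0.50 × 0.50/378 + 0.53 × 0.47/378) = 0.036. The 95% interval is 0.03 ± 1.96 × 0.036, or −4.1 to +10.1 points. A denominator that may be near zero or negative makes the ratio unstable, whereas net benefit remains defined.

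**The case against.** The strongest reply is that the article leaves more open than a critical reader might infer. Four stronger readings are tempting, and the document does not support them.

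- **That the ICER definitely uses the raw difference.** This is the likely reading, because logistic regression yields an odds ratio and no standardised risk difference is named. But adjustment of the proportions is planned, and a marginal risk difference can be taken from that same model. Confounding of the denominator is therefore conditional. Confounding of the costs does not depend on this, since the method named for them is a plain t-test.
- **That the two parts certainly cover different people, by a factor of 5.** The ICER sentence restricts neither part, and Sample size calculation sizes cost-effectiveness on participants with pre-diabetes, hypertension or diabetes, which may point to one diagnosed population. The mismatch is the natural reading of a cost for each Scheme participant, but it remains an inference. The factor of 5 borrows a prevalence meant for the comparison group.
- **That the ICER will have no interval.** The article is silent, and interval methods are commonly left to an analysis plan. This is not an error. An imprecise effect reflects the sample size and would remain after any change to how the ICER is built.
- **That operating costs are lost.** The article says that "ongoing operational costs would be collected over a 1-year period", ending December 2024, while the cohort enrolled January to April 2024 is followed into 2025. Nothing says that later costs count as zero, and a year of operating cost can supply a unit cost for each participant's own 12 months. This is not an error either.

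**Conclusion.** The concern holds in a limited form. What the document fixes is an unadjusted cost comparison between non-randomised groups, beside an adjusted comparison of the effect. If the plan is followed, the primary cost outcome and the ICER numerator are open to confounding. The denominator is too if the crude difference is used. The size of the bias cannot be derived from the article.

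The ICER wording also permits a mismatch of populations. If costs are not restricted to diagnosed participants, the ratio is understated by 1/q relative to an all-enrolee ICER: 5-fold at q = 20% and 1.25-fold at q = 80%. This rests on an assumed q, no effect among people who screen normal, and an equal diagnosed share in the two groups.

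The decision rule, as stated, sets a point ICER against the threshold. That is a reason to say how uncertainty enters the conclusion, not evidence that it has been ignored. The point deserves correction before analysis.

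**What to change.** 1. **Costs:** estimate the incremental cost by regression with the same confounders as the outcome model, in place of the t-test. This requires those covariates to be available for both groups.
2. **Effect:** state that the ICER denominator is the marginal (standardised) risk difference from the planned logistic model.
3. **Population:** define both parts on one population. Either use all enrolees, with the effect counted as additional participants at target per enrolee, or use diagnosed participants, with their costs plus the screening cost per case found.
4. **Decision:** base the cost-effectiveness conclusion on a joint bootstrap of cost and effect, reported as incremental net benefit at the stated threshold, with the ICER alongside.

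The cost is more analysis work on data already planned. The result may be less precise and less favourable to the Scheme.

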## Aims and objectives

This study aims to evaluate the quality of care, acceptability, effectiveness and cost-effectiveness of the CDCC Pilot Scheme. The objectives of this study are to:

Measure the adherence to the standards of care criteria by healthcare providers participating in the Scheme;Evaluate participant acceptability by self-reported outcomes on enablement, experience and satisfaction level about the services of the Scheme;Evaluate the effectiveness of the Scheme in improving health outcomes among CDCC participants over 12 months; and.Determine the provider costs and cost-effectiveness for delivering the CDCC Pilot Scheme relative to its effectiveness on participants health outcomes.

We hypothesize that:

Healthcare providers participating in the Scheme would achieve over 70% adherence for the standards of care criteria;60% of participants will report an increase in patient enablement levels after 12 months;90% of participants will report patient satisfaction 12 months after enrolment;A greater proportion of participants in the CDCC Pilot Scheme would achieve targets for disease control outcomes after 12 months compared to the comparison group; and.The Scheme would be cost-effective based on an incremental cost-effectiveness ratio (ICER) lower than the willingness-to-pay threshold of 1 annual gross domestic product (GDP) per person.

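### The cost-effectiveness rule compares the ICER with the threshold without regard to sign, so a costlier Scheme with worse disease control would meet the hypothesis

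*Protocol article*

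**What the plan says.** All references are to the protocol article.

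- **Direction of the rule (Aims and objectives, last hypothesis).** The Scheme counts as cost-effective on an "incremental cost-effectiveness ratio (ICER) lower than the willingness-to-pay threshold of 1 annual gross domestic product (GDP) per person".
- **Definition of the ratio (Data analysis).** The ICER is the "incremental cost incurred for each participant of the CDCC Pilot Scheme divided by the difference in the proportion of participants meeting targeted disease outcome".
- **Verdict (Data analysis).** "Cost-effectiveness of the Scheme would be determined by comparing the ICER to the willing-to-pay threshold of 1 GDP per year".

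The ICER is also listed as a primary outcome. Better disease control in the CDCC group is a separate hypothesis and is not made a precondition of the cost-effectiveness verdict. The p < 0.05 criterion is not tied to the ICER. The text shown does not say how a negative ratio, or a positive ratio with both terms negative, would be read.

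**The concern.** A ratio does not show which of its two terms is negative. A negative ICER can mean cheaper and better, or costlier and worse. A positive ICER can mean paying for a gain, or saving at the price of a loss. A bare comparison with a positive threshold treats the members of each pair alike.

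The verdict is a named hypothesis meant to inform primary care planning. A negative estimate of dE is not remote. The sample size section rests on a small effect: "Assuming a conservative 3% increase in the proportion of participants achieving treatment target after 12 months in the CDCC group". The comparison is also between non-randomised groups, and the comparators are screened and asked to follow up abnormal results themselves. If dE comes out negative, the rule as written can report success for a Scheme that was estimated to cost more and achieve less.

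**Working it through.** **1. The rule against net benefit.** Let λ be the threshold. The stated rule passes the Scheme if dC/dE < λ. Net benefit passes it if λ·dE − dC > 0.

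- If dE > 0, multiplying by dE keeps the inequality: dC < λ·dE. The two rules agree.
- If dE < 0, multiplying by dE reverses it: the stated rule passes when dC > λ·dE, that is, when net benefit is negative. The two rules give opposite verdicts.
- If dE = 0, the ICER is undefined.

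Examples, with cost in units of λ and dE = −0.03:

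| dC | ICER | Stated rule | Net benefit | Correct verdict |
|---|---|---|---|---|
| +0.02 | −0.67 | pass | −0.03 − 0.02 = −0.05 | fail |
| −0.01 | +0.33 | pass | −0.03 + 0.01 = −0.02 | fail |
| −0.05 | +1.67 | fail | −0.03 + 0.05 = +0.02 | pass |

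**2. Inputs for the size.** The plan states no error rate for this rule, so there is no figure of its own to reproduce.

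- Group size: the plan's 378 in total gives 378/2 = 189 per group. Its 1,886 comparators, with 20% prevalence and 30% attrition, give 1,886 × 0.20 × 0.70 = 264. The number of CDCC participants is not stated, so it is set equal (assumption). Whether 378 is enough for a 3-point difference is a separate question.
- Comparator proportion at target: not stated; 50% assumed.
- Incremental cost, cost SD and GDP: not stated. dC is taken as 1% to 15% of λ, with a per-person cost SD of 5% of λ (assumption).

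**3. How often dE is negative.** The standard error is √(2 × 0.5 × 0.5/n): 0.051 at n = 189 and 0.044 at n = 264. From the difference of two binomials:

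| True dE | n = 189 | n = 264 |
|---|---|---|
| +3 points | 26% | 23% |
| 0 | 48% | 48% |

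The no-effect figure is below 50% because 3-4% of studies give exactly dE = 0. By step 1, every study with dE < 0 gets the wrong verdict. Where the Scheme is estimated to cost more, that wrong verdict is always a pass.

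**4. Total passing rate with no effect.** For dC > 0 the rule passes if dE < 0 or dE > dC/λ. The normal approximation is 0.5 + 1 − Φ((dC/λ)/se). At n = 264 and dC = 5% of λ this is 0.5 + 1 − Φ(1.15) = 0.625. The binomial model, in which ties do not pass and cost is random, gives:

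| dC as share of λ | Stated rule, n = 189 | Stated rule, n = 264 | Net benefit > 0, n = 264 |
|---|---|---|---|
| 1% | 90% | 89% | 41% |
| 2% | 83% | 81% | 32% |
| 5% | 65% | 61% | 13% |
| 10% | 51% | 49% | 1% |
| 15% | 48% | 48% | under 1% |

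In each row at n = 264 the gap between the two rules is about 48 points, which is the share of studies with dE < 0.

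**5. Passing rate of the stated rule by true effect (n = 264).**

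| dC as share of λ | −3 points | 0 | +3 points | +10 points |
|---|---|---|---|---|
| 1% | 92% | 89% | 91% | 99% |
| 5% | 77% | 61% | 56% | 88% |

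**The case against.** The best defence is that the text presupposes a gain. Data analysis describes the ICER as the extra cost of one more participant reaching target, and a negative quotient from a costlier, worse Scheme is no such cost. The hypothesis just before it expects better control. The verdict sentence speaks only of comparing; the direction comes from Aims and objectives. Disease control and direct medical costs are separate primary outcomes, so a reader would see a lower proportion at target beside any ICER. Labelling a result as dominated is routine in economic evaluation, and a fuller plan may provide for it.

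Much of this stands as mitigation. A careful analyst would probably not announce success for a dominated Scheme. It does not remove the defect. The criterion is stated in two places, and the point concerns what that criterion returns, not a missing detail. Presupposing a gain does not require one, and nothing shown makes dE > 0 a condition.

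Three stronger readings are tempting and are not supported:

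- A reader might infer that a useless Scheme passes in well over half of studies. That depends on the incremental cost, which the documents do not give; at 10-15% of the threshold the rate is about 48-51%.
- A reader might infer that the less effective the Scheme, the more surely it passes. The last table shows that the rate is not monotone: among the effects shown, +10 points passes most often.
- A reader might cite the Background's expected savings as evidence that cheaper-but-worse is likely. The Background attributes savings partly to fewer complications, which means cheaper and better, where the rule is right.

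**Conclusion.** The point holds. Taken together, the two sections define a rule that passes a costlier Scheme with a lower proportion at target, and that gives the reverse of the correct verdict whenever the estimate of dE is negative. This follows from the algebra and needs no assumption.

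Its size does rest on assumptions: 50% at target and 189 to 264 per group. On these, the affected share is about 23-26% of studies if the planned 3-point benefit is real and about 48% if there is no effect. All of them pass wrongly if the Scheme costs more. The total no-effect passing rate is about 61-90% for an incremental cost of 1-5% of GDP per person and about 48-51% at 10-15%.

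Part of the lower-cost figures has another source: the verdict uses a point estimate alone. Even a net-benefit rule would pass about 41% of no-effect studies at a 1% cost if no uncertainty were considered.

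**What to change.** In Aims and objectives and in Data analysis, base the verdict on incremental net benefit: the Scheme is cost-effective if threshold × dE − dC > 0. Report it with a bootstrap confidence interval or the probability that it is positive, since the sign of the point estimate alone is weak evidence.

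Report the ICER only when dC and dE are both positive. Otherwise label the result:

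- dominated (costs more, no gain): not cost-effective;
- dominant (costs less, no loss): cost-effective;
- cost saving with health loss: cost-effective only if the saving per outcome lost exceeds the threshold.

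The change uses the same dC, dE and threshold and needs no new data or participants. It costs a few sentences and a little more analysis work. The downside for the study team is that a negative ICER no longer meets the hypothesis automatically.
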